### Study hypotheses

The principal hypothesis of this study is that ketamine IM provides similar efficacy to active treatment in patients with TRD due to a comparison between the experimental intervention (ketamine IM) vs. active treatment (escitalopram and aripiprazole). Other objectives of the study include confirming the safety and tolerability of the use of ketamine IM during acute and maintenance treatment.

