### Randomization and allocation

Randomization will be based on a computer-generated scheme, balanced by the use of randomly permutated blocks and stratified by the statistician of the Institute of Psychiatry of the FMUSP to receive ketamine IM or active treatment at a 1:1 ratio (82).

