### Sample size calculation

The sample size was calculated based on a similarly designed RCT (45). Assuming a statistical power of 90% with a clinically significant minimum effect of 0.5 (Cohen's d) and alpha 5%, a total of 88 subjects will be needed (44 in the EG and 44 in the CG). Given this is a long-duration study, a drop-out rate of 10–20% was estimated.

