### Statistical analysis

All analyzes will be performed using the Statistical Package for the Social Sciences-SPSS® (82). Specific and sociodemographic variables will be expressed generally and between intervention groups in relative and absolute frequencies, means, medians, standard deviation, and 95% confidence interval. Continuous variables will be evaluated by the *T*-student or U-Mann Whitney-test according to their distribution and the qualitative ones by the *X*^2^-test. The distribution of variables will be evaluated using the Shapiro Wilk. The global significance level adopted is 0.05. To determine the effects of intervention throughout the study (main outcome and other scales), repeated measures ANOVA (two-way) will be applied, considering the temporal effect of visits (v-0 to v-final) and the intervention effect (EG × CG). In identifying the significant interaction effect, one-way repeated measures ANOVA test or its non-parametric alternative (Friedmann test) will be performed to verify that the effect is independent of treatment. Contingency tables and *X*^2^-tests will be applied to compare responders and non-responders in the intervention groups. Analysis using intent-to-treat (ITT) will be employed to assess the results (83). Vital signs will be assessed using two repeated measures ANOVA (two-way). First, considering the effect of the intervention immediately (3 evaluations at each visit) and the second, evaluating the effect of the intervention on VS over time (acute and maintenance treatment).

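### The follow-up to a significant arm-by-visit interaction is given a purpose that contradicts its trigger and that the named tests cannot serve

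*Protocol article*

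**What the plan says.** All of the analysis text is in the Statistical analysis section of the protocol article.

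- Scope: "To determine the effects of intervention throughout the study (main outcome and other scales"), so the rule covers MADRS, the primary outcome, and the secondary scales.
- Main model: "repeated measures ANOVA (two-way) will be applied, considering the temporal effect of visits (v-0 to v-final) and the intervention effect (EG × CG").
- Trigger for the next step: "In identifying the significant interaction effect".
- Next step and its purpose: a "one-way repeated measures ANOVA test or its non-parametric alternative (Friedmann test) will be performed to verify that the effect is independent of treatment".
- Alpha: "The global significance level adopted is 0.05". Sidedness is not stated.

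The section also names t or Mann-Whitney tests for continuous variables in general and chi-square tests for responders by arm. Neither is presented as the follow-up to the interaction.

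Under Study hypotheses, the question is a between-arm one: "The principal hypothesis of this study is that ketamine IM provides similar efficacy to active treatment in patients with TRD".

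**The concern.** There are two faults in the same sentence.

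First, the step runs only when the arm-by-visit interaction is significant, which means the data have just given evidence that the arms follow different courses. A check that the effect does not depend on treatment is then aimed at the opposite of what triggered it.

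Second, a one-way repeated-measures ANOVA and a Friedman test each have one factor, visit. Their null hypothesis is no change over visits. With no arm in the test, no result can speak for or against a treatment difference.

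At stake is how the primary result is read. Patients in both arms may well improve over the visits. If both arms then show a significant time effect under a label of treatment independence, a reader could take this as support for the principal hypothesis of similar efficacy, just after the interaction has indicated a difference.

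**Working it through.** The plan states no figure on this point, so there is none to reproduce. The check is mainly one of logic, followed by two illustrations.

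**1. What each test asks.** Write μ(a,v) for the mean score in arm a at visit v.

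- Interaction in the two-way model. Null: μ(EG,v) − μ(CG,v) is the same at every visit. Rejection means that the course over visits differs by arm.
- One-way test run within arm a. Null: μ(a,v) is the same at every visit. The other arm does not appear.
- One-way test run on both arms pooled. Null: the average over arms is the same at every visit. Arm does not appear.

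The article does not say whether the one-way test is run per arm or pooled. Per arm is the natural reading after an interaction, but the conclusion is the same either way.

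**2. How easily a within-arm change reaches significance (illustration).** Changes in MADRS from baseline to day 15 are those quoted in the Introduction from a placebo-controlled IV ketamine trial. The n is from Sample size calculation: "a total of 88 subjects will be needed (44 in the EG and 44 in the CG"). The formula is t = mean change / (SD / √44), with √44 = 6.633 and 43 degrees of freedom, two-sided.

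| Group in the cited trial | Calculation | t |
|---|---|---|
| Placebo, twice weekly | 5.7 / (10.2 / 6.633) | 3.7 (p = 0.0006) |
| Placebo, three times weekly | 3.1 / (5.7 / 6.633) | 3.6 (p = 0.0008) |
| Ketamine, twice weekly | 18.4 / (12.0 / 6.633) | 10.2 |
| Ketamine, three times weekly | 17.7 / (7.3 / 6.633) | 16.1 |

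All four are significant, yet the between-arm gaps are 18.4 − 5.7 = 12.7 and 17.7 − 3.1 = 14.6 points. Significance in both arms is therefore compatible with a large difference between them.

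**3. The planned types of test (simulation).** Assumptions, none of them from the documents: 5 visits, SD 1, within-patient correlation 0.5, linear change, 4,000 runs, alpha 0.05. There were 44 patients per arm, as planned.

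| True fall in the two arms | Interaction significant | Both within-arm ANOVAs significant | Both significant, among runs with a significant interaction |
|---|---|---|---|
| 2 SD and 2 SD (identical) | 4.4% | 100% | 100% |
| 2 SD and 1 SD | 99.4% | 100% | 100% |
| 1.5 SD and 1 SD | 53% | 100% | 100% |

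Friedman tests gave the same picture (both significant in 100%, 100% and 99.95% of all runs). The last column matches the plan's conditional rule: once the interaction is significant, the follow-up gives the same answer whether the arms truly differ or the interaction was a false positive.

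With a small identical fall of 0.35 SD in both arms, exactly one arm reached significance in 51% of all runs (Friedman 48%), while the interaction was significant in 4.8%. The 51% is over all runs, not only those that would trigger the follow-up. It shows that a discordant pattern between arms is no evidence of a difference either.

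**The case against.** The strongest reply is that little depends on this sentence. The two-way ANOVA comes first, contains the arm factor and is retained. The follow-up runs only after that between-arm test has been done, and nothing says it can overturn the result. The clause may be a wording or translation slip for simple effects of time within each arm, which are a common follow-up and legitimate as description. **This stands as to consequence.** It does not rescue the clause: simple time effects would neither locate nor estimate the difference between arms, and the stated purpose would still be wrong.

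Three stronger readings are tempting, and the documents do not support them.

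- A reader might infer that the plan replaces the randomised comparison with two before-after analyses. It does not, because the arm-by-visit test is kept.
- A reader might infer that the effect will be declared independent of treatment if both arms are significant. No such decision rule is written, and no comparison of significance patterns is announced.
- A reader might infer that the plan will give no estimate of the treatment effect. That would rest on silence. An article may leave contrast visits and estimates to the full protocol or analysis plan.

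The borrowed t values also have limits. They come from IV ketamine against placebo at day 15 and use one-sample change tests, not the planned ANOVA or Friedman test over all visits. The control here is active, and the documents give no expected change for it.

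**Conclusion.** The sentence is wrong as written and should be corrected. Its purpose contradicts its trigger, and the tests it names cannot serve that purpose, however they are run. This conclusion rests on the tests' null hypotheses alone and needs no numerical assumption.

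The size is limited. The primary two-way test remains valid in principle, and the randomisation, data collection and responder comparison are untouched. What is exposed is the interpretation of a significant interaction, for MADRS and for every scale analysed in the same way. The risk is a misreading that favours the stated hypothesis. The t values and simulation results show how uninformative within-arm significance is; they do not measure an error in this trial's eventual conclusion.

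**What to change.** Delete the clause on independence of treatment. Replace the follow-up with EG–CG contrasts in MADRS change taken from the same two-way model, each with a 95% confidence interval, at a small number of prespecified visits and with a stated multiplicity rule.

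V-11 and V-35 are one workable choice. Both already appear under Measures and outcome variables. If visits are counted from v-0, the 12 acute injections end at V-11 and the 24 weekly ones at V-35 (12 + 24 = 36 visits, v-0 to v-35). Other visits or another multiplicity rule would also be defensible.

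Report within-arm time effects, if wanted, as descriptive only. Apply the same wording to the other scales.

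These contrasts would show where and by how much the arms differ. Without a margin they would not by themselves establish similar efficacy.

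The cost is one sentence in the protocol or analysis plan and no extra data. As the trial is already running, the change should be dated and made before unblinding.

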### Intervention

Two groups will be formed: a study group and an active control group. The study group will receive dextroketamine chloralhydrate IM (0.75 mg/kg) plus 2 placebo tablets orally, one in the morning and the other at night. The active control group will receive saline solution IM plus one of the alternative therapies for TRD: escitalopram 15 mg (morning) or aripiprazole 5 mg (night) (10). Injections will be applied alternately to gluteal muscles in the external upper quadrants. For 4 weeks (1 month), applications will be applied on Mondays, Wednesdays, and Fridays (giving a total of 12 interventions). For the ensuing 6 months, applications will be weekly (giving a total of 24 interventions). For 4 weeks (1 month), participants will continue to receive the tablets (active treatment or placebo) and be monitored. Safety parameters: vital signs will be monitored continuously by the researchers for 2 h post-application: fingertip pulse oximetry, heart rate, breathing rate, blood pressure, and electrocardiography. Abnormal blood pressure will be defined as low <90/60 mmHg and high >140/90 mmHg. Abnormal heart rate will be defined as <60 or >100 bpm. Abnormal breathing rate will be defined as <10 cycles/min or >20 cycles/min. Low oxygen saturation will be defined as levels <95%. Collateral symptoms such as nausea and vomiting will be managed using ondansetron 8 mg sublingually (SL). Individuals presenting episodes of anxiety, hallucinations, or intense dissociative effects will be given clonazepam SL 0.25 mg. An emergency team will be deployed in the event of serious acute events such as heart arrhythmia or prolonged hypertension. Patients will be placed under observation in a quiet comfortable environment and will be cleared to leave after 2 h, accompanied by a competent adult.

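### The only vital-signs analysis named compares means and does not use the protocol's own abnormality limits, so a non-significant result cannot support confirming safety

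*Protocol article*

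**What the plan says.** In the protocol article, the Intervention section lists safety parameters monitored continuously for two hours after each injection and gives numerical limits for each. For blood pressure: "Abnormal blood pressure will be defined as low <90/60 mmHg and high >140/90 mmHg". Heart rate is abnormal below 60 or above 100 bpm, breathing rate below 10 or above 20 cycles/min, and saturation below 95%.

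The Statistical analysis section then fixes the method: "Vital signs will be assessed using two repeated measures ANOVA (two-way"). The first ANOVA is described as "considering the effect of the intervention immediately (3 evaluations at each visit"); the second looks at vital signs over the acute and maintenance treatment. Neither refers to the limits.

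The scales are handled the same way: "To determine the effects of intervention throughout the study (main outcome and other scales), repeated measures ANOVA (two-way) will be applied". By the Measures and outcome variables section, the scales include CADSS (dissociation), YMRS (manic switching), BPRS item 12 (psychotic symptoms) and UKU-SERS (side effects).

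The Study hypotheses section sets the aim: "Other objectives of the study include confirming the safety and tolerability of the use of ketamine IM during acute and maintenance treatment".

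**The concern.** The limits classify individual values, and the named analysis estimates differences in averages. A safety question about vital signs is usually how many patients, and how many injections, went outside the limits and by how much. If three patients in 44 have a large rise and the rest none, the arm mean hardly moves. The same applies to YMRS, BPRS item 12 and UKU-SERS, whose stated purpose is to detect a switch, a symptom or a side effect.

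Attrition could add to this. The withdrawal section has prolonged hypertension and abnormal heart rate assessed for possible withdrawal. Classical repeated-measures ANOVA drops patients with incomplete series, so unless missing visits are handled in some other way, the analysis over time could lose the very patients affected.

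At stake is the safety and tolerability objective. A null comparison of means would say little about excursions in a minority.

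**Working it through.** The article states no safety figure, so there is none to reproduce. The calculations below illustrate what a comparison of means can detect.

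**From the article:** 44 patients per arm; three evaluations per visit; 12 acute and 24 maintenance injections, 36 in all; drop-out 10–20%.

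**Assumed, not in the article:** between-patient SD 12 mmHg; within-patient SD 5 to 8 mmHg; a 40 mmHg spike at one of the three readings of a visit in 5%, 10% or 15% of ketamine patients, and none in controls.

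**1. Dilution.** If a proportion p of patients spikes at one of three readings, the mean over the visit moves by p × 40 / 3. For p = 5%, 10%, 15% this is 0.7, 1.3 and 2.0 mmHg. The standard error of the difference between arms, ignoring within-patient noise, is √(2 × 12² / 44) = 2.56 mmHg. The shifts are thus 0.26, 0.52 and 0.78 standard errors.

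**2. Rejection rates for one visit.** Simulation, 5,000 trials per setting, two-sided 5%. Ranges cover within-patient SD 8 to 5.

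| Ketamine patients with a spike | Main effect, spikes at same reading | Group × time, spikes at same reading | Group × time, random timing |
|---|---|---|---|
| 5% | 6% | 10–16% | about 5% |
| 10% | 8% | 28–43% | about 5% |
| 15% | 11% | 49–71% | about 5% |

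The main effect is much the same under random timing (5–6%, 7–8% and 10–11%). The interaction depends wholly on timing.

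**3. A rise lasting all three readings.** Three of 44 patients with an assumed 50 mmHg rise move the mean by 3/44 × 50 = 3.4 mmHg. With SD 10–15, power is about 11–22%, from a t-test simulation and a normal approximation together.

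**4. What a count gives.** The expected numbers in the scenarios of step 2 are 44 × 0.05 = 2.2, 44 × 0.10 = 4.4 and 44 × 0.15 = 6.6 patients. Exact results against 0/44 in control:

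| Ketamine patients | Percentage (exact 95% CI) | Fisher p |
|---|---|---|
| 2/44 | 4.5% (0.6–15.5) | 0.49 |
| 3/44 | 6.8% (1.4–18.7) | 0.24 |
| 4/44 | 9.1% (2.5–21.7) | 0.12 |
| 5/44 | 11.4% (3.8–24.6) | 0.055 |
| 6/44 | 13.6% (5.2–27.4) | 0.026 |

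Fisher's test would reject in about 2%, 27% and 66% of trials in the three scenarios, so it is no more powerful than the interaction term at its best.

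**5. No events at all.** The one-sided 95% upper limit is 1 − 0.05^(1/n): 6.6% for n = 44, 7.2% for n = 40 and 8.2% for n = 35 (the last two roughly match 10% and 20% drop-out). The two-sided limit for n = 44 is 1 − 0.025^(1/44) = 8.0%.

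**6. Saturation of a patient-level count.** If an injection had an assumed 2–5% chance of any out-of-limit value, independently, the share of patients with at least one is 1 − (1 − q)^m: 22–46% over 12 injections, 38–71% over 24 and 52–84% over 36, in either arm.

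**The case against.** The strongest reply has four parts.

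First, this is a condensed article, and tables of out-of-limit values are ordinary SAP content. The section also has a general rule comparing continuous variables "according to their distribution and the qualitative ones by the" chi-square test, and abnormal yes/no is a qualitative variable. This stands in part: absence of such tables would not be a finding by itself. But the article does assign vital signs to a specific method, and neither the general rule nor the contingency tables, which are named for responders, is tied to the limits.

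Second, a reader might infer that the trial disregards dangerous excursions. The documents do not support that. The limits mark values as abnormal and include mild deviations. Patients are monitored for two hours with an emergency team available, and serious adverse events, prolonged hypertension and abnormal heart rate are assessed individually. The gap is in the group analysis, not in patient care.

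Third, a reader might infer that the trial will declare safety on a non-significant ANOVA. No such rule is stated. The concern is only that the objective's wording invites that reading and the named analysis could not bear it.

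Fourth, saying the ANOVA has almost no power would be too strong. That fits the main effect, but the planned two-way layout includes a group-by-time term, which does much better if excursions cluster at one reading. Counts do not win on power either, and over 36 injections a patient-level count may saturate. All of this stands, and it shapes the remedy.

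**Conclusion.** The point holds in a limited form. The article defines abnormality limits for four vital signs and then names, as their only analysis, two ANOVAs on means that do not use them. That is an ill-fitting method for a stated objective, not merely a detail left for later.

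The size depends on assumptions. With a 40 mmHg spike in 5–15% of ketamine patients, the main effect detects it in 6–11% of trials; the interaction detects it in about 10–70% if spikes coincide and about 5% if they do not. The spike, the SDs and the event rates are illustrations, not figures from the article. The analysis over time would dilute a spike further if it occurred at only a few visits.

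A non-significant ANOVA therefore cannot support confirming safety, and with 44 per arm no other analysis could confirm it against uncommon events. The zero-event limits of 6.6% and 8.0% reflect the sample size and are not a fault of ANOVA. What a count adds is a visible number with an interval.

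**What to change.** **Statistical analysis section.** Keep the ANOVAs. Beside them, add a descriptive comparison by arm of:

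- the number and percentage of injections with at least one post-injection value newly outside the Intervention section's limits, relative to the pre-injection value;
- the number and percentage of patients with at least one such value, separately for the acute and maintenance phases, because a single count over 36 injections may saturate.

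Give exact 95% confidence intervals for the patient percentages and the risk difference between arms with its interval. Injections from one patient are correlated, so the interval for injections should allow for clustering. State whether one of the three evaluations is taken before the injection. The article does not say, and the definition of newly abnormal needs it.

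For CADSS, YMRS, BPRS item 12 and UKU-SERS, report the distribution by arm of each patient's maximum score.

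**Study hypotheses section.** Replace the aim of confirming safety and tolerability with estimating them, and note the upper limit that zero events in 44 patients would leave.

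**Cost.** A few more tables, largely from data already recorded, low power for any formal comparison of counts, and a more modest safety claim. No clinical rule or limit changes.

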### Cognitive assessments

Neuropsychological tests will be applied at P0 and upon conclusion of PIII: to evaluate changes resulting from treatments:

**(1) Digit span (subtest of Wechsler Intelligence Scale):** measures attention span capacity and working memory; **(2) Wisconsin Card Sorting Test-64:** evaluate mental flexibility and ability to form abstract concepts in rapidly changing situations; **(3) Stroop Color-Word Test** (84): analyzes the maintenance of inhibitory control, from the suppression of the usual response in favor of an unusual response; **(4) Wechsler Abbreviated Scale of Intelligence (WASI):** the IQ is obtained from the sum of the gross results of the subtests converted to results weighted according to the individual's age (85); **(5) Verbal Fluency Test:** measures the ability to spontaneously produce words under semantic restriction and mind control (86); **(6) Rey's Complex Figure:** analyzes the visual-constructive ability, the ability to plan and problem-solving strategies (87) and; **(7) Trail-Making Test:** The purpose of this test is to assess alternate attention.

### Reasons for withdrawal or termination

Subjects who meet one or more of the criteria outlined below will be withdrawn from the study:

Intolerance to medications;Abnormal results on lab tests;Serious adverse event;The above-mentioned items will be assessed individually by the team according to medical criteria. Prolonged arterial hypertension, serious allergies, abnormal heart rate, or worsening of pre-existing diseases, among others, will be checked. Manic switching, imminent risk of suicide, attempted suicide, severe psychotic symptoms, aggressiveness, etc. will constitute grounds for study withdrawal.Relapse or lack of response in Phases II or III. Lack of response will be defined as reduction or maintenance of scores on the index scale of ≤25%, whereas relapse will be the attainment of scores <50% in individuals who had achieved remission or response during the study.Two consecutive visits missed;Withdrawal of consent for the study.

Patients who discontinue the study shall be given guidance to continue outpatient psychiatric treatment.

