The safety of ketamine has been confirmed for some decades, with anesthetic doses of 4–5 mg/kg intramuscularly (IM) proving effective [93–100% of children (1,022 pediatric cases)] for airways, emesis, or agitation (46). In a small number of patients, the drug can temporarily affect heart rate, and blood pressure and promote myocardial ischemia, although these risks can be attenuated by the use of sub-anesthetic doses and careful patient selection (27, 41, 44, 47). Dissociative states, a common side effect of the drug, are transient (lasting ~40 min, 2 h after use) and are not associated with persistent psychosis or mood swings (48). Of 158 patients given ketamine, 21 (13.3%) withdrew from the study, compared to 10 (7.4%) out of the 135 patients receiving control interventions (OR 1.95, 95%CI 0.86–4.42, *z* = 1.59, *p* = 0.11) (39). Claims that NMDA receptor blocking can cause “brain damage” and that ketamine affects the urinary retract remain the subject of controversy (49). The most common (≥20%) adverse events following the use of the drug include, headache, anxiety, dissociation, nausea, dizziness, and drowsiness on days of the administration, with these effects dissipating within 2 h, while more serious side effects leading to hospitalization or suicide attempts are rare (40, 50, 51). Anti-depressant effects of ketamine are short-lived (days or weeks), although longer-term benefits can be maintained by use of repeat doses, warranting further studies on the prolonged effects of the drug (44, 52). Intranasal (IN) esketamine was approved for use in 2019 by both the U.S. Food and Drug Administration (FDA) and the European Medicines Agency (EMA) (53). Other administration routes have also been investigated: IN, subcutaneous (SC), and oral (54–56).

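### Safety scales are compared by repeated-measures ANOVA over all visits, yet the harms they should detect end a patient's participation; intent-to-treat is not reconciled with this

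*Protocol article*

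**What the plan says.** Under Study hypotheses, a stated objective is "confirming the safety and tolerability of the use of ketamine IM during acute and maintenance treatment". Under Measures and outcome variables, four scales serve it: YMRS for manic switching, sub-item 12 of the BPRS for psychotic symptoms, CADSS for dissociation and UKU-SERS for side effects. Each is scored about one hour after every injection, in the acute phase (PII) and the maintenance phase (PIII) only.

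Under Statistical analysis, one method covers all scales: "To determine the effects of intervention throughout the study (main outcome and other scales), repeated measures ANOVA (two-way) will be applied". Its two factors are visit, running from the first to the last, and treatment arm. The same paragraph adds "Analysis using intent-to-treat (ITT) will be employed to assess the results (83"), describes variables by frequencies, and tests categorical variables by chi-square ("and the qualitative ones by the *X*^2^-test"). It names no adverse event or withdrawal reason for that test. The software is SPSS.

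Under Reasons for withdrawal or termination, patients leave the study, not only the treatment, for intolerance, abnormal laboratory results or serious adverse events, each judged individually. The list continues: "Manic switching, imminent risk of suicide, attempted suicide, severe psychotic symptoms, aggressiveness, etc. will constitute grounds for study withdrawal". Those who leave are directed to outpatient care, and no later study assessment is mentioned.

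**The concern.** For mania, psychosis and intolerance, the event that a scale exists to detect is also the event that ends the patient's data. A method that needs complete visits then compares only patients who tolerated treatment throughout. An arm that loses more patients to harm would show cleaner scale means, and the comparison would understate its harms. At stake is the objective of confirming safety and tolerability over seven months of treatment. What matters there is how many patients had a serious psychiatric or medical event, and a comparison of visit means does not answer that.

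**Working it through.** The protocol gives no figure to reproduce here. The check sets the sections side by side and then illustrates the size.

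**1. What each section fixes**

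| Section | What it fixes |
|---|---|
| Measures and outcome variables | Scales intended to detect events, scored after each injection |
| Statistical analysis | Comparison of means across all visits by arm |
| Reasons for withdrawal or termination | The same events remove the patient from the study |
| Statistical analysis (ITT sentence) | Who is analysed, but not what score a withdrawn patient has later |

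**2. How many visits must be complete.** The Intervention section gives 12 acute and 24 maintenance injections: 12 + 24 = 36 safety-scale visits. Classical repeated-measures ANOVA drops a patient with a score missing at any of them, so withdrawal before visit 36 removes the whole record.

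**3. Illustration.** All inputs except the 44 per arm and the 36 visits are assumed. Suppose *k* of 44 patients in one arm are harmed and none in the other. A harmed patient's score is 17 points higher at the event visit, and the patient is then withdrawn. The event visit is equally likely to be any of visits 1 to 35, so its average is visit 18, which leaves 36 − 18 + 1 = 19 visits at or after the event.

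- Complete cases: the harmed patients are deleted, so the expected difference is 0. A simulation of 1,000 trials per row gave 0.02, −0.01, 0.01 and 0.01.
- Last score carried forward: expected difference = (*k*/44) × 17 × (19/36). For *k* = 3 this is 0.0682 × 17 × 0.528 = 0.61. The simulation gave 0.2, 0.6, 1.0 and 1.9.
- Count: *k*/44, with an exact (Clopper–Pearson) 95% interval.

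| Harmed of 44 | Complete-case difference | Carried-forward difference (formula) | Patients harmed (exact 95% CI) |
|---|---|---|---|
| 1 | about 0 | 0.20 | 2.3% (0.1 to 12.0) |
| 3 | about 0 | 0.61 | 6.8% (1.4 to 18.7) |
| 5 | about 0 | 1.02 | 11.4% (3.8 to 24.6) |
| 9 | about 0 | 1.84 | 20.5% (9.8 to 35.3) |

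The first method loses the events. The second keeps them but spreads them over 44 patients and 36 visits, so the number harmed cannot be read from the result.

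**4. Which arm.** The only withdrawal figures by arm are in the Introduction: "Of 158 patients given ketamine, 21 (13.3%) withdrew from the study, compared to 10 (7.4%) out of the 135 patients" on control interventions. Applied to 44 per arm, 0.133 × 44 = 5.9 and 0.074 × 44 = 3.3 patients. These are withdrawals with no reason given, and the same sentence reports an odds ratio of 1.95 (95% CI 0.86 to 4.42, p = 0.11). They show a plausible scale of loss, not a direction for harm.

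**The case against.** The strongest reply is that the plan promises intent-to-treat. If that means filling in later scores, harmed patients stay in the comparison. This stands in part: loss of the harms is likely under the named method but not certain. The sentence still does not say how it is met with an ANOVA that needs every visit, and carrying scores forward leaves the dilution shown above.

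Second, the plan gives frequencies by arm and a chi-square test for categorical variables, lists suicide attempts and psychiatric admissions among the clinical history items, and commits to CONSORT. A condensed article may leave adverse-event tables to the full protocol. That is fair, so a reader should not infer that harms will go uncounted. The point rests on the method the article does fix for the safety scales.

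Third, two details limit the reach. Suicide risk is judged clinically and by HAM-D at entry, not by the four safety scales, so it belongs with the event count rather than the scale argument. The four scales also stop at the end of PIII, so the last relevant visit is the last maintenance injection, not the final visit of the trial.

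Fourth, a reader might infer that the plan is tilted towards finding ketamine tolerable. The document does not support this. The withdrawal rules apply to both arms, the control is an active drug treatment, and the cited withdrawal difference is all-cause and not significant.

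**Conclusion.** The point holds as a mismatch between three things the article itself fixes: repeated-measures ANOVA for the safety scales, withdrawal from the study for the harms those scales detect, and intent-to-treat. Without imputation, patients withdrawn for manic switching, severe psychotic symptoms, intolerance or a serious adverse event drop out of the scale comparison, including any score taken at the event visit. In the illustration, even 9 harmed of 44 gives a complete-case difference of about 0, against 1.84 points when scores are carried forward. The sizes depend on the assumed 17-point rise, on harm in one arm only and on uniform timing; the mechanism does not. The bias favours the arm that loses more patients to harm, and which arm that will be is unknown. The stronger statement that the worst harms are certain to vanish is not supported, because the intent-to-treat sentence could be carried out in a way that keeps them. The change is worth making because safety and tolerability are a stated objective and the remedy is cheap.

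**What to change.** In the Statistical analysis section, beside the scale means:

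1. Report by arm, among all patients who received at least one injection, the number with manic switch, psychotic symptoms, suicide attempt or imminent suicide risk, serious adverse event, or withdrawal for intolerance. Give exact 95% confidence intervals and a risk difference. This also captures events that arise between injection visits, when no scale score may exist.
2. For YMRS, BPRS sub-item 12, CADSS and UKU-SERS, compare each patient's worst score up to and including the withdrawal visit. Show the number of scored visits by arm, since fewer visits give fewer chances of a high score.
3. Analyse the repeated scores with a method that keeps patients with incomplete visits, for example a mixed model, so that it agrees with the stated intent-to-treat principle. The scale means can remain a planned comparison; they should not be the only one.

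The cost is a few more lines of analysis on scores already planned and on withdrawal reasons. No extra visits are needed, and no withdrawal rule changes.
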